### Study design

2.2

This is a multi-center, randomized, double-blind, parallel-group, placebo-controlled clinical trial. The trial has been initiated by the Guangdong Provincial Hospital of Chinese Medicine. After a 1-week run-in period, a total of 160 eligible participants are randomized to the treatment group (*Cordyceps militaris* capsules) or the control group (placebo capsules) in a 1:1 ratio. Participants receive a 24-week intervention and an additional 24-week follow-up period. Study visits will take place at baseline and weeks 12, 24, 36, and 48 within 30 days of each scheduled visit. Participants are required to provide written informed consent. The protocol follows the principles of the Standard Protocol Items: Recommendations for Interventional Trials (SPIRIT) Guidelines. A flowchart of the trial is shown in Figure 1. The schedule of enrollment, interventions, and assessments is presented in Table 1.

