#### Withdrawal/termination criteria

2.3.6

Participants are withdrawn from the trial if they meet any of the following criteria.Serious adverse events (SAEs) related to the investigational treatment occur.Serious complications, allergic reactions, clinically significant liver or kidney dysfunction, significant physiological changes that occur during the trial.Continued participation poses unacceptable risks to the participant, as judged by the principal investigator.Participants who experience recurrent infections during treatment will be withdrawn under the automatic withdrawal criteria. Specifically, if a participant experiences two or more acute exacerbations within 1 month requiring emergency department visits or hospitalization, the participant will be automatically withdrawn from the study to mitigate the risk of clinical deterioration and safeguard participant welfare.

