### Sample size calculation

2.6

The sample size has been calculated using PASS software (Version 15.0.5) based on a superiority test design, with assumptions derived from prior subgroup analyses of *Cordyceps militaris* capsules in the treatment of COPD. The primary endpoint is the change in the post-bronchodilator FEV_1_, with an assumed mean difference of 110 mL between groups, and standard deviations set at 250 mL for the treatment group and 201 mL for the control group (Shergis et al., 2019). A one-sided superiority test is conducted with α = 0.025 and Power = 1-β = 0.90, assuming equal allocation between groups. The sample size calculation indicates that 68 participants per group (N = 136) are required to detect the specified treatment effect. To accommodate an anticipated 15% attrition rate, the final sample size is increased to 160 participants (80 per group).

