### Outcomes and measurements

2.8

The time points of the study data collection for outcome measurements are shown in Table 1.

The primary outcome is change in the post-bronchodilator FEV_1_. Lung function assessments are performed once each at baseline, weeks 12, 24, 36, and 48. Secondary outcomes include additional lung function parameters, such as pre-bronchodilator FEV_1_, pre- and post-bronchodilator measures of FVC, FEV_1_/FVC ratio, mid-expiratory flow (MMEF), forced expiratory flow 75% (FEF75) and forced expiratory flow 50% (FEF50). In addition, frequency of acute exacerbations, time to the first acute exacerbation, COPD Assessment Test (CAT), Cough and Sputum Assessment Questionnaire (CASA-Q), EuroQol five-dimension five-level questionnaire (EQ-5D-5L), and Modified Medical Research Council dyspnea scale (mMRC) are also included. These outcomes are also measured once each at baseline, weeks 12, 24, 36 and 48.

Blood, sputum and stool samples are collected from at least 60 participants enrolled in the Guangzhou center for metagenomics (airway and intestinal flora), transcriptomics, metabolomics, proteomics analyses and induced sputum cell classification. Biological samples are collected at baseline, weeks 24 and 48 after treatment, following standard operating procedures for acquisition, processing, and cryopreservation.

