### Statistical analysis

2.11

The analysis will be performed using the intention-to-treat principle on the full analysis set, with additional analyses conducted on the per-protocol set and safety set. Only authorized study personnel will be able to view and manage data. The between-group comparison of acute exacerbation frequency will be conducted using a Poisson regression model that includes treatment group as the independent variable, annualized exacerbation rate as the dependent variable, and stratified randomization factors as adjustment covariates. Least squares means with corresponding 95% confidence intervals (with appropriate transformations when required) will be estimated from the specified model to evaluate between-group differences. Continuous variables will be analyzed using appropriate parametric (two-sample t-test or adjusted t-test) or nonparametric (Wilcoxon rank-sum test) methods, while categorical variables will be evaluated using either Pearson’s chi-square test or Fisher’s exact test. Time-to-event endpoints will be analyzed using Kaplan-Meier methodology, with median event times and interquartile ranges (IQR, 25th-75th percentiles) estimated for each group. Between-group differences will be assessed using log-rank tests. For missing data, the last observation carried forward method will be employed for imputation. For the center effect analysis, continuous variables will be analyzed using analysis of covariance or meta-analysis, while categorical variables will be assessed using Cochran-Mantel-Haenszel statistics.

Baseline demographic and clinical characteristics, including age, sex, disease duration, smoking status, smoking index, medical history, and concomitant medications, will be summarized descriptively and assessed for balance between groups. When appropriate, adjusted analyses will be conducted by including these variables as covariates in multivariable models to reduce the impact of potential confounding factors on treatment effect estimation. In addition, prespecified subgroup analyses stratified by sex will be performed to explore potential differences in treatment response to *Cordyceps militaris* capsules.

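### LOCF is the only missing-data method named; it can bias the FEV1 difference in either direction, and a repeated-measures model on visits already collected should replace it

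*Protocol article*

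**What the plan says.** Section 2.11 (Statistical analysis) states: "For missing data, the last observation carried forward method will be employed for imputation". The sentence is not limited to an endpoint, a visit or an analysis set, and the article names no other method. The same section says "The analysis will be performed using the intention-to-treat principle on the full analysis set", so participants who leave stay in the analysis with imputed values. It adds "Continuous variables will be analyzed using appropriate parametric (two-sample t-test or adjusted t-test) or nonparametric (Wilcoxon rank-sum test) methods", so those values enter the test as if they had been observed.

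The features of the trial that bear on this are:
- Section 2.8: "The primary outcome is change in the post-bronchodilator FEV_1", with no primary time point in that sentence, and "Lung function assessments are performed once each at baseline, weeks 12, 24, 36, and 48".
- Section 2.2: "Participants receive a 24-week intervention and an additional 24-week follow-up period". Weeks 36 and 48 are therefore off treatment.
- Section 2.6: "To accommodate an anticipated 15% attrition rate, the final sample size is increased to 160 participants (80 per group").
- Section 2.3.6: after two or more exacerbations within a month that need emergency or hospital care, "the participant will be automatically withdrawn from the study to mitigate the risk of clinical deterioration".
- Section 1 (Introduction): FEV1 falls by 49-60 mL/year in mild-to-moderate disease.

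**The concern.** LOCF assumes that a participant's FEV1 stops changing on the day of the last visit. That conflicts with the article's own account of progressive decline. It also conflicts with the treatment hypothesis, under which FEV1 in the active arm changes over the 24 weeks.

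Three groups are affected:
- Someone lost before week 12 has only a baseline value. If kept in the full analysis set with baseline carried forward, that person gets a change of exactly zero.
- Someone withdrawn under section 2.3.6 keeps a value that may predate the exacerbations that caused the withdrawal.
- Someone lost after week 24 has an on-treatment value entered at weeks 36 and 48.

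The estimate then depends partly on when people leave, and the size and sign of the error follow the dropout pattern. What is at stake is the accuracy of the main FEV1 difference and of any claim that benefit lasts after treatment stops.

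**Working it through.** **Inputs from the article.** Difference 110 mL; SDs 250 and 201 mL; 80 per arm; attrition 15% (all section 2.6). Visits at weeks 12, 24, 36 and 48 (section 2.8). Decline 49-60 mL/year (section 1).

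**The plan's own attrition figure.** 68 / 0.85 = 80 per arm, which reproduces. Expected losses are 0.15 × 160 = 24 participants. (The 68 per arm does not reproduce at the stated 90% power. That is a separate matter and does not affect what follows.)

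**Step 1: decline omitted by freezing.** Rate × weeks / 52, per imputed participant:
- 12 weeks: 11-14 mL
- 24 weeks: 23-28 mL
- 48 weeks: 45-55 mL

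At week 24 with 15% imputed from baseline, this is 0.15 × 23 to 0.15 × 28, or about 3-4 mL per arm. It cancels if both arms lose the same share. If 25% versus 5% are missing and all are frozen at baseline, the difference at week 48 shifts by 0.20 × 45 to 0.20 × 55, about 9-11 mL.

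**Step 2: week 24, true effect 110 mL, 15% lost in each arm.** Assumptions not in the article: half the effect (55 mL) is reached by week 12; baseline is carried forward for those lost earlier; dropout is unrelated to outcome; dropouts would have reached the full effect. Expected LOCF difference:
- All lost before week 12: 0.85 × 110 = 93.5 mL
- Half before, half after: 93.5 + 0.075 × 55 = 97.6 mL
- All lost after week 12: 93.5 + 0.15 × 55 = 101.8 mL

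Simulation (20,000 runs, within-patient correlation assumed 0.7) gave 94, 98 and 102 mL, with coverage 0.923, 0.936 and 0.943. Without missing data it gave 110 mL and 0.951. Power fell from 0.86 to about 0.80.

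**Step 3: source of the undercoverage.** The mean standard error (SE) matched the actual spread of the estimator: 33.1 vs 33.1, 34.5 vs 34.5 and 35.8 vs 36.0 mL. Coverage can be predicted from bias alone as Φ(1.96 − b) − Φ(−1.96 − b), where b = bias / SE:
- 16.5 / 33.1 = 0.50 gives 0.921
- 12.4 / 34.5 = 0.36 gives 0.935
- 8.25 / 35.8 = 0.23 gives 0.944

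These agree with the simulation, so bias explains the shortfall.

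**Step 4: no treatment effect.** With the same decline in both arms and equal 15% dropout, bias was 0.5 mL or less and one-sided type I error 0.025-0.026. With 25% lost on treatment and 5% on control (assumed), the week-48 difference was +7 mL.

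**Step 5: week 48, effect fully lost after the drug stops (true difference 0).** With 10% lost after week 24 in each arm (assumed): 0.10 × 110 = 11 mL. A separate simulation with dropout spread over all visits and assumed mean trajectories gave +7 mL at 15%/15% (coverage 0.946) and +19 mL at 25%/5% (coverage 0.916).

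**The case against.** **The shortfall at week 24 depends on the estimand.** The 94-102 mL figures count as biased only if the target is the effect dropouts would have reached on treatment. If people who stop the drug lose its benefit, 0.85 × 110 = 93.5 mL could be the right answer, and a jump-to-reference imputation gives about that figure when all leave before week 12. This stands as a limit on the numbers, but it does not rescue LOCF. Under that target the answer is 93.5 mL whenever people leave, while LOCF gives 93.5, 97.6 or 101.8 mL depending on timing. It tracks neither target.

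**Natural decline does not produce those figures.** Step 1 puts it at 3-4 mL per arm at week 24, cancelling under equal dropout. This stands: the attenuation comes from freezing the treatment response, and decline matters when dropout is unequal.

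**The worst cases rest on undefined terms.** The article does not define the full analysis set. If it requires a post-baseline value, only the 102 mL case remains. Nor does section 2.6 say whether the 15% accrues by week 24 or week 48. Both stand.

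**Stronger readings a reader might infer.**
- That LOCF also understates uncertainty. With early dropout the mean SE (33.1 mL) is below the no-missing-data value, √((250² + 201²) / 80) = 35.9 mL, which looks like false precision. But it matches the estimator's own spread, so no separate defect is shown.
- That LOCF inflates the false-positive rate. Step 4 shows it does not under equal dropout and equal trajectories; the article gives no ground for assuming unequal dropout.
- That LOCF governs the exacerbation outcomes. Section 2.11 already gives these an annualized-rate Poisson model, Kaplan-Meier estimates and log-rank tests. The unrestricted sentence needs only a clarifying limit.
- That off-treatment carry-over contaminates the primary result. This happens only if the primary contrast uses week 36 or 48, and section 2.8 names no time point.

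The number of withdrawals under section 2.3.6 cannot be estimated, because no rate is given. The absence of a stated sensitivity analysis is ordinary matter for an analysis plan and is not counted here.

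**Conclusion.** The concern holds as a should-fix point. LOCF is fixed in the text, and its assumption of constant FEV1 after dropout contradicts the article's own premises. It can move the FEV1 difference either way: towards zero at week 24 when a real effect builds up over time, and away from zero at week 48 when the effect fades or when dropout is unequal.

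The likely size is moderate. At week 24 the loss is about 8 to 16 mL out of 110 mL, with coverage of 0.92-0.94 and power about 0.06 lower. At week 48 the false benefit is about 11 mL, roughly 0.3 of a standard error. These sizes rest on the assumptions in the working about trajectory, dropout timing, retention of early losses and the target of estimation, none of which the article states. The documents do not support saying that the primary estimate will be biased, or that its sign of error is known.

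**What to change.** For FEV1 and the other continuous repeated measures, replace the LOCF sentence with a mixed model for repeated measures on all observed visits. Include treatment, visit, treatment-by-visit, the baseline value and GOLD stratum, with unstructured covariance. Take the week-24 contrast as the main result; weeks 36 and 48 come from the same model.

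Add one sensitivity analysis by reference-based or delta-adjusted multiple imputation, aimed at outcome-related withdrawal. State that LOCF does not apply to exacerbation counts or time to first exacerbation, which keep the follow-up-time and censoring methods already named.

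The cost is revised analysis text and a little programming. No new data or visits are needed. Section 2.3.1 expects recruitment to finish in late 2026 and the trial in late 2027, so the change can be made before database lock. The main analysis would then rest on a missing-at-random assumption, which the sensitivity analysis is there to test.

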### Randomization and allocation

2.4

The randomization sequence has been generated using a central randomization system. The randomization procedure was programmed using SAS 9.2 software to generate the randomization sequence. In this study, stratified block randomization was designed with airflow limitation severity (GOLD I and GOLD II) as the stratification factor. The researchers use a centralized randomization system to perform participant allocation. Participants are allocated to either the treatment or control group in a 1:1 ratio. The statistical unit maintains centralized control over all study identifiers (center numbers, sequence assignments, randomization codes, and drug numbers) to preserve blinding and prevent bias.

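### Sex differences in response are to be explored by analyses within each sex, which do not assess a difference between the sexes; a treatment-by-sex interaction estimate would (minor, exploratory)

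*Protocol article*

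**What the plan says.** Protocol article, section 2.11 (Statistical analysis), last sentence of the paragraph on baseline characteristics: "prespecified subgroup analyses stratified by sex will be performed to explore potential differences in treatment response".

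The same section sets the methods for continuous outcomes, which include the primary outcome: "Continuous variables will be analyzed using appropriate parametric (two-sample t-test or adjusted t-test) or nonparametric (Wilcoxon rank-sum test) methods". It also allows multivariable models, when appropriate, with baseline variables including sex as covariates. It mentions no product term between treatment and sex. It gives no significance level for the sex analysis and no rule for claiming a sex difference.

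Section 2.4 (Randomization and allocation) stratifies with "airflow limitation severity (GOLD I and GOLD II) as the stratification factor". Sex is not a stratification factor. The article gives no expected sex split.

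**The concern.** The aim is a question about a difference between two effects: does the drug change post-bronchodilator FEV1 by a different amount in men and in women? The natural reading of the method is a treatment comparison in men and another in women. Each of those asks whether there is an effect in that sex. Neither estimates the difference between the sexes, so the method does not answer the stated question.

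Two separate results invite comparison of their p-values. Each sex has fewer patients than the whole trial, and the less common sex may have very few. One significant and one non-significant result is then a frequent chance finding even when the drug acts equally in both sexes. A sex difference reported from an analysis labelled prespecified would carry more weight than it deserves.

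**Working it through.** **Inputs.** Section 2.6 (Sample size calculation) gives the effect ("with an assumed mean difference of 110 mL between groups"), the spread ("standard deviations set at 250 mL for the treatment group and 201 mL for the control group"), the test ("A one-sided superiority test is conducted with α = 0.025 and Power = 1-β = 0.90") and the evaluable number ("68 participants per group (N = 136) are required to detect the specified treatment effect"), raised to 80 per group for 15% attrition. The following are assumptions: the larger sex is 50% to 90% of patients; the sexes are balanced across arms; both sexes have the same true effect and SDs; and the one-sided 0.025 level carries over to the within-sex tests.

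**The plan's own figure first.** The sum of variances is 250² + 201² = 102,901. The normal formula gives n per group = (1.96 + 1.2816)² × 102,901 / 110² = 89.4, so 90 (91 by Welch t), not 68. Power at 68 per group is about 80%. The attrition step does reproduce: 68 / 0.85 = 80. The mismatch in the sample size is a separate matter. Here 68 is used as the stated evaluable number, and 80 and 91 are checked as well.

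**Power within one sex.** With m patients per arm in that sex, SE = √(102,901 / m) and power ≈ Φ(110/SE − 1.96). For an 80:20 split of 68 per arm:
- Larger sex, m = 54.4: SE = 43.5, power = Φ(0.57) = 0.715.
- Smaller sex, m = 13.6: SE = 87.0, power = Φ(−0.70) = 0.243.

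**Chance that exactly one sex is significant.** The two tests use different patients and so are independent. With powers p₁ and p₂ the chance is p₁(1 − p₂) + p₂(1 − p₁). At 80:20 this is 0.715 × 0.757 + 0.243 × 0.285 = 0.61.

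The table uses the Welch t version, 110 mL in both sexes and 68 per arm:

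| Sex split | Power, larger sex | Power, smaller sex | Exactly one significant |
|---|---|---|---|
| 50:50 | 0.504 | 0.504 | 50% |
| 60:40 | 0.580 | 0.418 | 51% |
| 70:30 | 0.648 | 0.326 | 55% |
| 80:20 | 0.707 | 0.228 | 61% |
| 90:10 | 0.758 | 0.127 | 69% |

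Simulation (20,000 trials per setting, whole patients) agrees: 50.3% at 50:50, 55.6% at 70:30 and 61.0% at 80:20.

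**Sensitivity to sample size.** Over 50:50 to 90:10, the range is 49% to 73% at 80 per arm and 46% to 75% at 91 per arm.

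**Sensitivity to the true effect** (68 per arm, 50:50 to 90:10): 42% to 49% at 80 mL, 28% to 29% at 55 mL, 11% at 22 mL and 5% at zero.

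**Interaction test on the same data.** At two-sided 5%, with the same 110 mL effect in both sexes, a false difference appeared in 4.9% to 6.3% of simulated trials (splits 50:50 to 85:15; 68 and 80 per arm).

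**Precision of the interaction.** SE = √(102,901 × (1/m₁ + 1/m₂)).
- 50:50 (34 and 34 per arm): SE = 78 mL, 95% CI half-width 1.96 × 78 = 153 mL, power for a true 110 mL sex difference Φ(110/77.8 − 1.96) = 29%.
- 80:20 (54.4 and 13.6 per arm): SE = 97 mL, half-width 1.96 × 97 = 190 mL, power Φ(110/97.3 − 1.96) = 20%.

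**The case against.** The strongest reply is that the article never states the rule modelled above. It does not say that two p-values will be compared, or that a sex difference will be declared when only one is significant. Analyses stratified by sex could mean an estimate and confidence interval for each sex, read descriptively, and that need not mislead anyone. The purpose is exploratory. A statistical analysis plan that is not shown may already contain an interaction test, and an article commonly leaves such detail to it. All of this stands, and it makes the figures conditional on one way of reading the results. It does not remove the mismatch: the article does state an aim and a method, and the method does not address the aim.

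Three stronger readings are tempting, but the documents do not support them.

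- A reader might infer that the plan will show a false sex difference more often than not. That needs a true effect near 110 mL, an unequal split and the significance-versus-non-significance reading. At an equal split the chance is 2p(1 − p), which cannot exceed 50%. At 80 mL or less it stays below 50% across the splits examined.
- A reader might infer that effective in men but not in women is the expected outcome. The discordance figures also count the opposite result. If men are the larger sex, the men-only result has probability 0.504 × 0.496 = 25% at 50:50, 0.648 × 0.674 = 44% at 70:30 and 0.707 × 0.772 = 55% at 80:20. It passes one half only at quite uneven splits, and the article gives no split.
- A reader might infer that a GOLD-grade subgroup is missing because randomization is stratified by it. Stratifying by a factor does not oblige a subgroup analysis by that factor.

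An interaction test would also have little power here. That is true, but the within-sex comparisons hold no more information about a sex difference; they only hide how little there is.

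**Conclusion.** The point holds as a minor one about an exploratory analysis. Within-sex comparisons do not assess the between-sex difference that section 2.11 sets out to explore, and an interaction estimate does so at almost no cost.

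If the two results were read by their significance, a common effect at the planning value would look like a sex difference in about half to seven in ten trials. At 55 to 80 mL it would do so in about three to five in ten. The interaction test does so in about one in twenty. These figures rest on the planning SDs, 68 evaluable per arm, assumed sex splits of 50:50 to 90:10 and one-sided 0.025 within each sex. They describe a risk that the wording leaves open, not a rule that the article lays down. The primary comparison is not affected.

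**What to change.** Replace the sentence on sex subgroups in section 2.11 with wording to this effect: the effect of sex on treatment response will be judged by the treatment-by-sex interaction estimate with its 95% CI, from a linear model of change in post-bronchodilator FEV1 containing treatment, sex and their product; effects and CIs within each sex will be descriptive, and no claim of a sex difference will rest on within-sex p-values. If the statistical analysis plan already says this, only the published wording needs aligning.

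The cost is one sentence and one linear model. The model must be named, because a t-test or Wilcoxon test cannot carry the interaction term. Conduct and sample size do not change, and section 2.3.1 expects recruitment to run to late 2026, so the wording can be settled before database lock. The downside is a wide interval: power is only about 20% to 29% for a 110 mL sex difference, so a non-significant interaction should not be reported as evidence that the sexes respond alike. No GOLD-grade subgroup is required.
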